## Abstract

**Background:**

Universal immunisation is the cornerstone of preventive medicine for children, The World Health Organisation (WHO) recommends diphtheria-tetanus-pertussis (DTP) vaccine administered at 6, 10 and 14 weeks of age as part of routine immunisation. However, globally, more than 17 unique DTP-containing vaccine schedules are in use. New vaccines for other diseases continue to be introduced into the infant immunisation schedule, resulting in an increasingly crowded schedule. The OptImms trial will assess whether antibody titres against pertussis and other antigens in childhood can be maintained whilst adjusting the current Expanded Programme on Immunisation (EPI) schedule to provide space for the introduction of new vaccines.

**Methods:**

The OptImms studies are two randomised, five-arm, non-inferiority clinical trials in Nepal and Uganda. Infants aged 6 weeks will be randomised to one of five primary vaccination schedules based on age at first DTwP-vaccination (6 versus 8 weeks of age), number of doses in the DTwP priming series (two versus three), and spacing of priming series vaccinations (4 versus 8 weeks). Additionally, participants will be randomised to receive their DTwP booster at 9 or 12 months of age. A further sub-study will compare the co-administration of typhoid vaccine with other routine vaccines at one year of age. The primary outcome is anti-pertussis toxin IgG antibodies measured at the time of the booster dose. Secondary outcomes include antibodies against other vaccine antigens in the primary schedule and their safety.

**Discussion:**

These data will provide key data to inform policy decisions on streamlining vaccination schedules in childhood.

**Trial registrations:**

ISRCTN12240140 (Nepa1, 7^th^ January 2021) and ISRCTN6036654 (Uganda, 17^th^ February 2021).

**Supplementary Information:**

The online version contains supplementary material available at 10.1186/s13063-023-07477-9.

## Background

Following the success of the smallpox eradication programme, the World Health Organisation Expanded Programme on Immunisation (WHO EPI) began in 1974, with the aim that all children in all countries could benefit from life-saving vaccines. At the time, the EPI included vaccination against six diseases: tuberculosis (BCG), diphtheria, tetanus and pertussis (DTP), measles and poliomyelitis. The list of recommended vaccines has since grown to include many new vaccines. Expansion of the immunisation schedules over the past two decades has significantly reduced death and morbidity among young children globally [1–3]. A substantial proportion of the protection is provided by herd immunity [4, 5]. In the future, new vaccines may be added to the EPI schedule, such as those for respiratory syncytial virus (RSV) and group B streptococcus.

Globally there are more than 17 unique DTP-containing schedules in use, with many countries aligning their schedules to regional norms. These include 2, 4, and 6 months (USA and the Americas); 2, 3, and 4 months (UK, western Europe, and central Asia); 6, 10, and 14 weeks (most of Africa and South Asia, recommended by WHO); 3, 5, and 12 months (Scandinavia and Italy); and 3, 4.5 and 6 months (Japan and China). Little evidence exists on the relative impact of these different schedules. Some evidence suggests that they may differ in key outcomes including immunogenicity, lasting protection, and acceptability by health workers and care-givers [6–8].

In 2009 the European Centre for Disease Control reviewed evidence for the optimal timing of DTP immunisation and due to the lack of available data, called for new studies to assess the differing schedules [9]. Four key research areas were highlighted: the optimal timing of the first DTP-containing vaccine, the number of doses in the priming series (two versus three), the interval between priming doses and lastly, the need for and timing of a booster dose to optimise immunity.

The current accelerated EPI schedule begins at 6 weeks of age and is designed to provide early protection against pertussis. However, there is a trade-off between earlier coverage and generation of strong immune responses due to the fact that weaker antibody responses to vaccination are seen in younger infants at this age [10]. Schedules which begin later and have longer intervals between doses are more immunogenic [11–13]. In reality, delivery of the EPI schedule on time is challenging for many countries; of 45 studied countries, the median delay for DTP1 was 2.4 weeks, and the median delay for DTP3 was 6.2 weeks [14].

Evidence from the trials of newer vaccines in infancy suggests that two doses given in a priming series may provide adequate protection. For example, pre-licensure trials of the 7-valent pneumococcal vaccine assessed 3 primary doses in the first 6 months of life and a 12-month booster [15]. However, this vaccine was successfully introduced to the UK in 2006 with a reduced 2-dose priming schedule at 2 and 4 months, and a 12-month booster, which was subsequently adjusted to a one dose priming schedule at 3 months of age with a booster at 12 months.

Nepal became the first Gavi-eligible country to adopt a variation on this schedule for the introduction of the 10-valent pneumococcal vaccine (6, 10 weeks and 9 months, with no further booster) reducing the number of injections, and total cost [16]. There is variability in the use of a booster for DTP, with some countries such as the UK, providing no booster until preschool age and others offering booster vaccinations at 12–18 months. The current accelerated WHO EPI schedule (6, 10, 14 weeks) does not include a booster dose. Currently, there is crowding of the vaccination schedule in early infancy due to the need to cover several differing antigens, with little room for new additions. However, it is likely that new childhood vaccines such as that for RSV are likely to require doses in early infancy if introduced [17].

There is a clear need for evidence to support optimisation of the current EPI schedule. The OptImms trials have been designed to identify an optimal immunisation schedule for infants by comparing the immunogenicity of 5 different priming immunisation schedules including the current WHO recommended schedule, and additional sub-studies comparing the impact of varied timing of booster doses, and co-administration of a typhoid conjugate vaccine (TCV) at one year of age.

## Methods

The OptImms trials are randomised, non-inferiority 5-arm clinical trials in Uganda and Nepal, using the WHO schedule as the reference schedule.

### Study sites

The Uganda site trial will take place at the Medical Research Council (MRC)/Uganda Virus Research Institute (UVRI) & London School of Hygiene and Tropical Medicine (LSHTM) Uganda Research Unit field site in the Greater Masaka area, Uganda. Masaka lies in the south-western Uganda region, approximately 120 kms from the capital city, Kampala. The population within the trial area is semi-urban, semi-rural. DTP1 coverage in Uganda was approximately 91% in 2019 with DTP3 coverage at 73% [18]. Infants will be enrolled at trial hubs located in three health facilities and clinics in the Masaka area. The Nepal site trial will take place in the two largest municipalities in the Kathmandu Valley: Lalitpur at Patan Academy of Health Sciences (PAHS), Patan Hospital and Kathmandu at the Institute of Medicine, Tribhuvan University Teaching Hospital (TUTH). The Kathmandu Valley is a large urban area with a high population density and is the largest urban area in Nepal. DTP1 coverage in Nepal, in 2019, was 96%, with DTP3 coverage at 93% [18, 19].

### Public engagement

Extensive community engagement has been taking place in both countries since 2019. The study teams will meet with local leaders, District and Municipality health teams, community members and in-country health and political leaders. The Uganda site has a well-established community advisory board who review the participant facing documents.

### Objectives

#### Primary objective

The primary objective of these studies is to identify a schedule (or schedules) that maintains early protection against pertussis prior to the booster dose and is equivalent to, or better, than the WHO EPI schedule.

#### Secondary objectives

Identify a schedule (or schedules) that maximises early protection against pertussis.Identify a schedule (or schedules) that maximises protection against tetanus, diphtheria, pertussis, hepatitis B, *Haemophilus influenzae* type b (Hib), and pneumococcus post booster dose.Identify a schedule (or schedules) that provides space in the immunisation programme for inclusion of new vaccines by minimising the number of diphtheria, tetanus, whole-cell pertussis, *Haemophilus influenzae* type b (Hib), hepatitis B virus (DTwP-HBV/Hib) doses (i.e. 2 priming doses rather than 3) whilst maintaining protectionIdentify a schedule (or schedules) that maximises long-term protection at 24 months of age by vaccines for pneumococcus and tetanus, diphtheria, pertussis, hepatitis B, and *Haemophilus influenzae* type b (Hib).Identify a schedule (or schedules) that maximises protection against tetanus, diphtheria, pertussis, hepatitis B, *Haemophilus influenzae* type b (Hib) and pneumococcus post-primary and pre-booster dose and polio (pre-booster only)Assess the optimal timing of delivery of a booster dose of DTwP-Hib/HBVAssess the effect of concomitant administration of typhoid conjugate vaccine with the Japanese encephalitis (JE)vaccine in Nepal and yellow fever (YF) vaccine in Uganda.

#### Exploratory objectives

Assess the optimal timing of measles-rubella vaccine administration

#### Safety objective

2.Assess the safety of alternative vaccination schedules in terms of reactogenicity post each vaccination dose

956 participants will be randomised to one of 5 primary schedules in each country:Arm 1: DTP at 6, 10 and 14 weeks (WHO EPI schedule)Arm 2: DTP at 6, 14 weeks + booster (modified WHO EPI)Arm 3: DTP at 2, 4 months + booster (OptImms schedule)Arm 4: DTP at 2, 3, 4 months (2–3–4 schedule)Arm 5: DTP at 2, 4, 6 months (2–4–6 schedule)

The chosen schedules (Table 1) compare how variation in timing, number of doses, dose interval and booster doses may affect immunogenicity and persistence of antibody generated in response to EPI vaccinations. Each schedule has been selected based on real-world use, globally, or immunogenicity data from previous studies: Arm 1 represents the WHO-recommended “accelerated” schedule and serves as the control arm for the purpose of statistical analyses. Arms 2 and 3 are two variations on the WHO 2 + 1 reduced priming schedule — one beginning at 6 weeks, and one with wider intervals between doses, beginning at 8 weeks. Arms 4 and 5 represent schedules used in the UK and the Americas, respectively.

**Table 1 Tab1:**
[figure not shown]
Main vaccine schedules for each primary vaccine arm and blood draw timepoints

In addition to randomisation to one of five main primary vaccination schedules, participants will be randomised to receive booster vaccines at one of two time points (9 months or 12 months) and in addition (1) concomitant TCV, (2) concomitant Japanese encephalitis (JE) (Nepal only) or YF (Uganda only), or (3) concomitant TCV with either JE (Nepal) or YF (Uganda).

The booster schedules will investigate the effect of the timing of the DTP-containing booster, as well as the immune response to the concomitant administration of TCV with other routine EPI vaccines (DTP, JE and/or YF) when administered together or separately.

### Randomisation

Participants will be electronically randomised to one of the 5 main primary vaccination arms in a ratio of 4:4:4:3:3, using block randomisation. This will take place within an eCRF hosted by REDCap (v11.1.8). For arms 1–4, a second randomisation will allocate participants to 1 of 4 booster groups, in a ratio of 3:1:1:1. For arm 5, participants will be allocated in a 1:1:1 ratio to booster groups 2–4 (see Table 2). Half of the study participants will be randomised to receive a DTP-containing booster at 9 months (Booster Group 1), together with the MR and PCV vaccinations already recommended by the WHO EPI at this timepoint. Participants in this booster group will then receive TCV vaccination at 10 months. The remaining half will be randomised to receive a DTP booster at 12 months of age, given either with both TCV and JE/YF, or one of these at 12 months and one at 13 months, to evaluate any effects of concomitant vaccine administration on immunogenicity.

**Table 2 Tab2:**
[figure not shown]
Booster group vaccine schedules and blood draw timepoints

To minimise the number of blood samples for each infant, participants will be randomised to receive 4 blood samples across the two-year follow-up period. The possible blood sample time points vary between the 5 main vaccination arms (Tables 1 and 2). All participants will have a blood sample taken 1-month post-priming series and pre-booster. Two additional blood samples will be taken: one during the priming series, and one during the booster series.

The following vaccine formulations to be administered in this trial will be the same across all sites and are outlined in Table 3 below. All other vaccines given in this trial will be in line with the vaccines currently used as part of the country’s immunisation programme.

**Table 3 Tab3:** Vaccine formulations to be administered in OptImms

Manufacturer	Vaccine	Contents
Serum Institute of India	DTwP-HBV-Hib	Diphtheria toxoid ≥ 30 IU, Tetanus toxoid ≥ 40 IU B. Pertussis (whole cell) ≥ 4 IU, Hep B surface antigen (rDNA) 10mcg, Purified capsular polysaccharide of Hib (PRP) conjugated to tetanus toxoid (carrier protein) 10mcg
Bharat-Biotech	Typhoid conjugate	Purified Vi-capsular polysaccharide of *S. Typhi* Ty2 conjugated to Tetanus Toxoid 25 µg
Sanofi Pasteur	Yellow fever	Yellow fever virus1 17D-204 strain (live, attenuated) not less than 1000 IU produced in specified pathogen-free chick embryos

Trial arm allocation will be open-label for participants, clinical trial staff and statisticians, but laboratory staff will be blinded.

### Participants

Parents/guardians of healthy children aged 42–50 days will be approached when they present for their 6-week immunisations. All healthy children, living in the study area, will be eligible for enrolment in the study. Children will be excluded if born prematurely (< 37 weeks gestation), at a low birth weight (< 2.5 kg), or presenting with serious health concerns, as determined by study medical staff (see Appendix).

### Enrolment

At the enrolment visit, children will go through a pre-screening process, including confirmation of age and birth weight with an assessment of temperature. Written and verbal versions of participant information and informed consent documentation will be provided to parents/guardians by trial staff including clinicians, health care staff and counsellors. Impartial witnesses will be used in cases where parents/guardians are unable to read participant information leaflets. Trial staff will inform the participants the study arm to which they have been allocated including time of booster doses and blood draw visits. Participants will be given the opportunity to ask questions about their allocated study arm, to ensure full understanding of the schedule to which they have been randomised. They will be asked to provide written informed consent by means of a signature or thumbprint.

The participant will be considered enrolled once the consent form is signed, eligibility criteria are met and the participant has been randomised into a trial arm. They will receive an OptImms-specific child health card aligned to the format of the local child health cards currently in use in the study country. This will include the immunisation schedule for the participant’s allocated trial arm, infant growth charts, infant health advice, and space for non-study vaccinations to be recorded.

### Benefits to participants

Free routine medical care and treatment of infections will be provided to all participants during the course of the study. Participants may also receive benefits from the administration of additional study vaccines not currently in the Nepal/Uganda EPI schedule; Yellow fever vaccine (currently recommended in Uganda but not offered routinely), typhoid conjugate vaccine administered during the booster phase of the study, and varicella vaccine which is offered to all participants at 2 years of age. Travel costs will be reimbursed for all participants at each visit.

### Study visits and participant follow-up

At each study visit, routine and study vaccines will be administered and/or study blood draws performed as per the allocated arm. Topical anaesthetic cream will be used at each blood draw visit to minimise pain, discomfort and distress for participants and their parents.

Participants will also receive follow-up phone calls from the study team, to maintain contact with participants and their families and to help ensure participants stay on their designated study schedule.

If a parent/guardian decides that they wish to withdraw from the trial, catch-up immunisation will be arranged by the local teams to ensure participants have not been disadvantaged by their participation in the study and that they have received immunisations in line with the national EPI schedule in that country.

For participants receiving a specific antigen schedule outside of the WHO recommendations, and where immunological data are available for that participant, an additional dose of the relevant vaccine will be offered to children who have not mounted an immune response to the accepted threshold of protection, measured one month after the final dose of that vaccine. For children who meet these criteria, this additional vaccine will be offered after the immunological data have been analysed, at the end of the study.

### Laboratory assays

Assays for both countries will be carried out in the same laboratory. Serum will be used for assessing immune responses to each component of the vaccines included in the study. This will be measured by multiplex immuno-assay, enzyme-linked immunosorbent assay (ELISA), plaque reduction neutralisation tests (PRNT), or indirect fluorescent antibody tests as applicable (Table 4).

**Table 4 Tab4:** Antigens and assays for primary and secondary immunogenicity outcomes

Antigen	Assay	Volume of serum required (µl)
Diphtheria toxin, tetanus toxin, pertussis (pertussis toxin, pertactin, filamentous hemagglutinin), Hib-PRP, hepatitis B surface antigen, polio types 1–3, pneumococcal antigen (all 10 serotypes)	Multiplexed immunoassay	150
Japanese encephalitis virus	Enzyme-linked immunosorbent assay	100
	Plaque reduction neutralisation titres/indirect fluorescent antibody assay	50
Yellow fever virus	Enzyme-linked immunosorbent assay	100
	Plaque reduction neutralisation titres	30–80
Typhoid Vi antigen	Enzyme-linked immunosorbent assay (IgG and IgA)	60–100

### Data management

Data will be collected via direct data entry, into the study REDCap database. Databases will be hosted on physically secure local servers within each study country, with data management oversight being led by the University of Oxford team in collaboration with local data teams. Study staff will be responsible for ensuring that participants’ confidentiality is maintained with identification only via a participant identifier on study documentation and databases. All study documentation in hard copy will be stored securely in line with Good Clinical Practice guidelines.

### Data analysis

The trial dataset will be made available to study statisticians. Primary outcome, anti-pertussis toxin IgG measured prior to the booster dose, will be assessed using a non-inferiority comparison. Primary analyses will be carried out by separately comparing Arms 2 and 3, to Arm 1. If the lower bound of the one-sided 95% confidence interval for the difference in log-geometric means for any group compared to Arm 1 excludes a standardised effect size of — − 0.35 (Cohen’s d) then non-inferiority will be deemed to have been demonstrated. In the primary analysis, we will present the results from both intention-to-treat and per-protocol analysis. Secondary and exploratory outcomes will either be analysed descriptively or using superiority comparisons unless specified otherwise in the statistical analysis plan. The trial will not directly evaluate whether there is an interaction between the primary vaccination series and vaccination with TCV and YF (Uganda) or JE (Nepal). There is no planned interim analysis and no formal stopping rules for this trial.

### Sample size

Based on recent publications on the trial vaccine DTwP-HBV-Hib (Serum Institute of India), we found that the geometric mean concentration (GMC) and standard deviation (SD) of anti-pertussis IgG vary between studies and there is no consensus on the threshold of protection [20–25]. The sample size calculation for this trial is based on a non-inferiority margin presented as a proportion change in units of standard deviation (SD), or Cohen’s D. Since the two main non-inferiority comparisons will be “Modified EPI” (Arm 2) and “OptImms” (Arm 3) vs “WHO EPI” (Arm 1), the type I error is set as 0.025. The assumptions for the power calculation are:Power of 90%Non-inferiority margin of 35% SDType I error of one-sided 0.025

Table 5 shows the non-inferiority margin based on different SDs in the current publications of the trial vaccine.

**Table 5 Tab5:** Non-inferiority margins based on varying standard deviations (SDs)

Standard deviation	Non-inferiority margin on Log_10_ scale
Standardised standard deviation (SD = 1) on the Log_10_ scale	− 0.35 (Cohen’s d)
Assuming an SD of 0.6 on the Log_10_ scale [20]	− 0.21 (equivalent to a GMR of 0.62)
Assuming an SD of 0.2 on the Log_10_ scale [23]	− 0.07 (equivalent to a GMR of 0.85)

A minimum of 782 children per country are required for a fully powered analysis of the primary outcome, therefore each country will recruit 956 children to allow for loss-to follow-up of approximately 15%.

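### The sizing alpha (0.025) and the decision bound (one-sided 95%) for the two primary comparisons disagree; a Holm step-down would reconcile them with more power than 0.025 for each arm and the same 5% error limit

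*Protocol article*

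**What the plan says.** The two relevant sections of the protocol article give different levels.

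- Sample size: with Arm 2 v Arm 1 and Arm 3 v Arm 1 named as the two main non-inferiority comparisons, "the type I error is set as 0.025". The listed assumptions are 90% power, a margin of 0.35 SD and a one-sided test. "A minimum of 782 children per country are required for a fully powered analysis of the primary outcome".
- Data analysis: "Primary analyses will be carried out by separately comparing Arms 2 and 3, to Arm 1". The decision rule follows: "If the lower bound of the one-sided 95% confidence interval for the difference in log-geometric means for any group compared to Arm 1" excludes −0.35, non-inferiority is taken as shown.

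Two other places matter. The Primary objective is to "identify a schedule (or schedules) that maintains early protection against pertussis", so more than one schedule may succeed. Randomisation allocates the five arms "in a ratio of 4:4:4:3:3, using block randomisation", so Arms 1 to 3 are equal in size and Arms 2 and 3 share one control.

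The article mentions neither a step-down procedure nor the power for both comparisons to succeed.

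**The concern.** The Sample size section ties 0.025 to the number of comparisons, so it works as a multiplicity adjustment. The decision rule does not carry that adjustment through, because a one-sided 95% bound for each arm is a test at 0.05 for each arm.

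The obvious repair is to use 97.5% bounds for both arms. That controls the error but is stricter than it needs to be. Once one schedule has passed at 0.025, the other can be tested at 0.05 without the familywise error exceeding 0.05. A reduced-dose schedule that is truly non-inferior would then fail less often. The primary result is the list of schedules that may be called non-inferior, so the choice of repair affects what policymakers can use.

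**Working it through.** **Inputs.** Margin 0.35 SD, one-sided 0.025, power 90% and 782 evaluable children (Sample size); allocation 4:4:4:3:3 (Randomisation); one-sided 95% bound (Data analysis). Assumptions: true difference 0, since none is stated; the 90% is per comparison; one analysis set decides; normal approximation.

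**Reproducing 782.** Per arm, n = 2(z₁₋α + z₀.₉₀)²/0.35².

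- α = 0.025: 2(1.960 + 1.282)²/0.1225 = 171.5, so 172, or 173 with the t distribution. With 174 per arm, 3 × 174 + 2 × 130 = 782 exactly.
- α = 0.05: 2(1.645 + 1.282)²/0.1225 = 139.8, so 140, and 140 × 18/4 = 630.

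The stated size therefore rests on 0.025 per comparison.

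**Set-up at 174 per arm.** SE = √(2/174) = 0.1072 SD, and 0.35/0.1072 = 3.265. With equal arms and a shared control, the two test statistics correlate at 0.5. Let Φ₂ be the bivariate normal distribution function with that correlation.

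- Distance above the 0.025 cut-off: 3.265 − 1.960 = 1.305.
- Distance above the 0.05 cut-off: 3.265 − 1.645 = 1.620.
- Φ(1.305) = 0.9040; Φ(1.620) = 0.9474.
- Φ₂(1.305, 1.305) = 0.8386; Φ₂(1.305, 1.620) = 0.8710; Φ₂(1.620, 1.620) = 0.9078.

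**Power under Holm.**

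- Both pass: 2 × 0.8710 − 0.8386 = 0.9034.
- Per comparison: 0.9040 + (0.8710 − 0.8386) = 0.9364.
- At least one passes: 2 × 0.9040 − 0.8386 = 0.9694, the same as with 0.025 each, because the first step is the same.

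**Familywise error, both arms at the margin.**

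- 0.025 each, or Holm: 1 − Φ₂(1.960, 1.960) = 0.045.
- 0.05 each: 1 − Φ₂(1.645, 1.645) = 0.088.

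Under Holm, with one arm at the margin and the other equal to control, the error is 0.0499, and it cannot exceed 0.05.

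| Rule | Per comparison | Both pass | At least one | Error, both at margin |
|---|---|---|---|---|
| 0.025 each | 90.4% | 83.9% | 96.9% | 4.5% |
| Holm (0.025, then 0.05) | 93.6% | 90.3% | 96.9% | 4.5% |
| 95% bound each, as written | 94.7% | 90.8% | 98.7% | 8.8% |

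Simulation with 400,000 runs agreed: 83.9%, 90.4% and 90.8% for both passing.

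**Sensitivity of both passing, 0.025 each v Holm.**

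- 172 per arm: 83.4% v 90.0%.
- 180 per arm (956 × 4/18 × 0.85 ≈ 180): 85.3% v 91.3%.
- Both reduced schedules truly 0.05 SD below control, 174 per arm: 68.6% v 78.6%.

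If one arm is equal to control and the other is 0.10 SD below, power for the weaker arm is 64.5% v 74.1%. With 0.025 each, about 206 per arm would be needed to reach 90.3% for both.

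**The case against.** **The gain is measured against a rule the article does not use to decide.** This stands. The written decision rule is the 95% bound for each arm. Against it, Holm slightly lowers the chance that both pass (90.8% to 90.3%) and that at least one passes (98.7% to 96.9%). What it gains there is error control.

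**The 0.025 split is valid, and the stated power is met.** This also stands. A reader might infer that the trial is underpowered because both arms pass only 84% of the time. The documents do not support that: no joint power target is stated, 90.4% per comparison meets the 90%, and a single successful schedule satisfies the primary objective.

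**A step-down rule is a detail for the analysis plan, and sizing at 0.025 does not exclude one.** The second half is right, since 0.025 is the first Holm step. The first half only partly answers the point, because the article itself fixes both an alpha and a decision rule, and the two conflict.

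**Separate 97.5% bounds match their claims; Holm's need not.** This is a real cost. Every additional joint success under Holm is a case where the second arm's 97.5% bound crosses −0.35 and only its 95% bound clears it. The report can handle this by showing which bound decided each claim, but a sponsor may reasonably prefer the simpler display.

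**Conclusion.** The point holds as an inexpensive improvement to make while the two sections are reconciled. The Sample size section is not in error.

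Compared with 0.025 for each arm, Holm adds about 3 percentage points of power per comparison (90.4% to 93.6%) and 6.5 points to the chance that both pass (83.9% to 90.3%, before rounding). The familywise limit stays at 5%, no children are added, and the chance of at least one success is unchanged. Compared with the 95% rule as written, there is no power gain, but the error with both arms at the margin falls from 8.8% to 4.5%. It would be wrong to read the result as six points of power missing from the plan as it stands.

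The power figures rest on 174 evaluable children in each of Arms 1 to 3 and a true difference of zero. The overall one-sided 0.05 is inferred from the reason given for 0.025. If the sponsor meant 0.025 as the overall level, the step levels would change. All figures apply within one country.

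**What to change.** State the same rule in the Data analysis and Sample size sections: within each country, Arms 2 and 3 are tested against Arm 1 by Holm at an overall one-sided 0.05.

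1. The arm with the smaller non-inferiority p-value must clear −0.35 SD with a one-sided 97.5% bound. If it does not, neither claim is made.
2. If it does, the other arm is tested against −0.35 SD with a one-sided 95% bound.

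Keep 782 evaluable and 956 recruited. Say outright that the overall level is one-sided 0.05 and that the 90% power is per comparison. Report the bound that decided each claim, and show 97.5% bounds for both arms as description. A step-down Dunnett procedure, which uses the shared control, would serve equally well. Statisticians are not blinded to allocation, so the rule should be fixed before they see assay results.

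The cost is one or two sentences and a somewhat less simple display. If the sponsor prefers matching bounds, one-sided 97.5% for both arms also resolves the conflict, at the lower power shown above.
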